#### Primary outcome

The primary outcome will be average pain intensity in the low back during the last 7 days, measured by the 0–10 Numerical Rating Scale (NRS) [41] ranging from 0 (complete absence of pain) to 10 (worst imaginable pain) (Table 2).

**Table 2 Tab2:** Detailed description of the outcome measures that will be assessed in the trial

Questionnaire/Test	Functions/Parameters	Description
**Musculoskeletal pain**^**a**^		
0–10 Numerical Rating Scale (NRS) for pain [41]	Pain intensity (average and worst)	Intensity during last 7 days (0–10)
Ad hoc question	Pain frequency	Days in pain during last 7 days (0–7)
Ad hoc question	Pain interference	Days in which pain negatively interferes with work during the last 7 days (0–7)
Ad hoc question	Pain medication consumption	Days of analgesic medication consumption during last 7 days (0–7)
**Psycho-affective state**		
Subjective Happiness Scale [42]	Happiness	4 items measuring perceived current happiness (1–7)
Goldberg Anxiety and Depression Scale [43]	Anxiety and depression	9 items measuring anxious (0–9) and 9 items measuring depressive (0–9) symptoms during last month
Maslach Burnout Inventory (MBI) [44]	Burnout	9, 5 and 8 items measuring frequency of feelings related to emotional exhaustion (0–54), depersonalization (0–30) and personal accomplishment (0–48), respectively
Single-Item Sleep Quality Scale [45]	Sleep quality	Single item measuring sleep quality during last 7 days (0–10)
Ad hoc question	Hypnotic/anxiolytic medication consumption	Days of hypnotic/anxiolytic medication consumption during last 7 days (0–7)
EuroQol-5D 0–100 Health State Scale [46]	Quality of life	Single item measuring self-perceived current health state (0–100)
**Work-related variables**		
Work Ability Score (WAS) [47]	Work ability	Single item measuring self-perceived current work ability (0–10)
World Health Organization Health and Work Performance Questionnaire (HPQ) [48]	Work performance	Single item measuring self-perceived work performance during last 7 days (0–10)
Borg’s CR-10 Scale [49]	Physical exertion at work	Single item measuring self-perceived physical exertion at work during last 7 days (0–10)
Institution’s registry and self-reported	Work absenteeism	Presence of absenteeism (yes/no), days of absence (n) and reason during last year

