## Methods

### Study design

A parallel-assignment, multicenter randomized controlled trial will be carried out. Participants will be recruited from institutions providing eldercare services at home or in long-term facilities. In each of the institutions, and following baseline measurements, participants will be randomly assigned (1:1 ratio) through sealed opaque envelopes to either a control or experimental group by a coin-tossing sequence generation. Assessments of primary and secondary outcomes will be conducted at baseline and at 12 weeks (post-supervised phase) and 48 weeks (post-unsupervised phase) from the beginning of the intervention (Fig. 1). Outcome assessors and data analysts will be blinded to group allocation. Because of the nature of the study, blinding of the participants and the professional supervising the sessions is not possible. The study was designed, and the results will be reported according to the SPIRIT statement [30] and CONSORT guidelines for trials of nonpharmacologic treatment interventions [31].

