### Inclusion and exclusion criteria

Subjects will be considered eligible for the study if they meet all the following criteria: (a) are formal eldercare workers from eldercare institutions, (b) are ≥ 18 years of age, (c) have ≥ 3 months of experience in the profession, and (d) have an employment contract until at least the date of study completion. Participants will be excluded if (a) they are pregnant or (b) their participation is considered contraindicated according to the American College of Sports Medicine’s exercise preparticipation health screening guidelines [32].

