#### Secondary outcomes

A detailed description of all the secondary outcomes is shown in Table 2. They will include validated questionnaires and tests for evaluating: (a) musculoskeletal pain [41] (intensity, frequency, and interference) of the low back, neck, shoulders and hands/wrists; (b) psycho-affective state [42–46] (subjective happiness, anxiety and depression, burnout, sleep quality, and quality of life) which will be collected by a self-administered written questionnaire; (c) work-related variables [47–49] (work ability, performance, physical exertion, and absenteeism) which will be obtained by a self-administered written questionnaire and from the official registry of the participating eldercare institution; and (d) physical fitness (trunk, lower and upper limbs muscle performance), which will be evaluated by a battery of physical performance tests [50–52] previously validated by our research group to be carried out remotely by real-time videoconference [53]. The participant's self-reported days of medication consumption of analgesics and hypnotics/anxiolytics during the last 7 days at each assessment point will also be recorded.

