### Statistical analysis plan

IBM SPSS Statistics 27 statistical software package (SPSS, Inc., Chicago, IL) will be used for data analysis. Normality of distribution will be checked using the Kolmogorov‒Smirnov test, and non-normally distributed variables will be square-root transformed for statistical analysis. Continuous and categorical data will be reported as mean (standard deviation) and frequency (percentage), respectively. The primary analysis will be based on intention-to-treat, including data from all participants regardless of adherence to the intervention. Additionally, a per-protocol analysis will be performed, including only data from participants with ≥ 50% adherence. Finally, a post-hoc subgroup analysis will be performed to assess the effects of the intervention on low back pain outcomes separately in participants with (≥ 1 in average 0–10 NRS) and without (< 1 in average 0–10 NRS) low back pain at baseline. Between-group comparisons at baseline will be performed with the independent samples T and Chi-squared tests for continuous and categorical variables, respectively. For continuous variables, intervention effects will be analyzed with a group-by-time ANCOVA including baseline measurements as covariates. This ANCOVA will be performed separately to assess intervention effects in two time periods: 0 vs 12 weeks and 0 vs 48 weeks. Within-group changes in each time period will be performed with the paired samples T test. Effect size will be estimated by partial eta squared (η^2^). Values for η^2^of 0.02, 0.13, and 0.26 will be considered small, medium and large, respectively [56]. For categorical variables, intervention effects will be analyzed with McNemar’s test. The level of statistical significance will be set at *p* < 0.05.

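### Days and presence of absence are scored over the last year without allowing for time observed, so before-after tests lean towards apparent worsening for workers whose prior year is incomplete

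*Protocol article*

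**What the plan says.** Under Work-related variables, Table 2 defines absenteeism as "Presence of absenteeism (yes/no), days of absence (n) and reason during last year". The source is given as "Institution’s registry and self-reported", and the Secondary outcomes section says that work-related variables come from a written questionnaire and "from the official registry of the participating eldercare institution". Neither place gives a rate or a denominator.

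Under Inclusion and exclusion criteria, workers must "have ≥ 3 months of experience in the profession" and "have an employment contract until at least the date of study completion". No minimum time with the current employer is set. Primary and secondary outcomes are assessed at baseline, 12 and 48 weeks (Study design).

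Under Statistical analysis plan, for continuous variables "intervention effects will be analyzed with a group-by-time ANCOVA including baseline measurements as covariates". In addition, "Within-group changes in each time period will be performed with the paired samples T test". For categorical variables the stated test of intervention effects is McNemar's test. Variables that are not normally distributed are to be square-root transformed.

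**The concern.** A 12-month look-back presumes 12 months in which absence could occur and be recorded. The entry rule does not guarantee this at baseline, whereas the contract rule makes a full or nearly full window likely at 48 weeks. Two kinds of worker are affected: those not employed for part of the prior year, and those in the institution's registry for less than 12 months whose earlier absence self-report does not recover. For them the two counts cover different lengths of time, and the later one is higher on average even if the absence rate is constant.

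The paired t test on days compares these two counts person by person. McNemar's test, also a paired before-after comparison, does the same for yes/no absence, and there it is the named test of the intervention. A real fall in the exercise arm could be partly hidden, or a stable control arm could appear to worsen. Absenteeism is a secondary outcome, but the sample size section justifies its target difference by relevance to absence from work, and the Discussion cites fewer lost work days in earlier exercise studies, so readers will look at it.

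**Working it through.** The article gives no figure for this point, so there is none to reproduce.

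**Inputs from the article.** Look-back of 12 months (Table 2); minimum of 3 months in the profession (Inclusion criteria); assessments at 0, 12 and 48 weeks (Study design); 65 per arm, or 52 after the 20% loss the article allows for (65 × 0.8).

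**Assumed, because the article does not give them.** The share *f* of workers whose prior year is incomplete, how their tenure is spread, and the distribution of absence days.

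**Coverage for one worker.** Covered share = min(1, time observed / 12 months).
- Baseline: 3/12 = 25%, 6/12 = 50%, 9/12 = 75%.
- Entry at 3 months (about 13 weeks), week 12: (13 + 12)/52 = 48%.
- Entry at 3 months, week 48: 13 + 48 = 61 weeks, more than 52, so 100%.

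At a constant rate, the expected count of a worker who entered at 3 months therefore rises 1/0.25 = 4-fold from baseline to week 48.

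**Yes/no for one worker.** At a constant hazard, P(3 months) = 1 − (1 − P(12 months))^0.25. A 12-month probability of 30% shows as 8.5% over 3 months; 50% shows as 15.9%.

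**Arm mean.** With mean covered share *c* among affected workers, the baseline mean is too low by *f*(1 − *c*), and the apparent rise is 1/[1 − *f*(1 − *c*)] − 1. Tenure spread evenly over 3 to 12 months has mean 7.5 months, so *c* = 7.5/12 = 0.625. If all are at 3 months, *c* = 0.25.

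| Share *f* | Baseline shortfall, spread tenure | Apparent rise, spread tenure | Apparent rise, all at 3 months |
|---|---|---|---|
| 10% | 3.8% | 3.9% | 8.1% |
| 20% | 7.5% | 8.1% | 17.6% |
| 30% | 11.3% | 12.7% | 29.0% |
| 50% | 18.8% | 23.1% | 60.0% |

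With spread tenure the shortfall passes 10% at *f* = 0.10/0.375 = 27%.

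**Tests under no true change.** One simulation used 52 workers in an arm, 0.7 absence spells a year with gamma frailty (variance 1), mean spell length 15 days, and 1,500 runs. With spread tenure:
- Paired t on raw days rejected 4.8%, 4.7%, 6.7% and 9.3% of the time at shares of 10, 20, 30 and 50%.
- After a square-root transform, the rates were about 6%, 5%, 7–8% and 11–12% (ranges over repeat runs).
- Exact McNemar, which is conservative (about 3% with no short-tenure workers), stayed near 3% up to a 20% share, was 4–5% at 30% and 6–8% at 50%.
- At a 50% share, mean days moved from 8.5 to 10.5 and presence from 35% to about 41–42%.

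With every affected worker at 3 months, the same model gave paired t 10% and McNemar 12% at a 30% share, and 23% and about 28% at a 50% share.

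A second model (65 per arm, days Poisson given a gamma-distributed personal rate with mean 10 a year, affected workers all at 3 months) gave paired t rejection of 15%, 44% and 76% at shares of 10, 20 and 30%. Days there do not cluster in spells, so within-person change is much less noisy and the same shift is detected more often. In that model the between-arm ANCOVA rejected 4.6% to 5.0% of the time, with a mean difference of about 0.

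**The case against.** The strongest reply is that the randomised comparison is sound. Short-tenure workers fall in both arms alike, and the ANCOVA on days, which is the intervention test for that variable, kept its error rate even in the worst case. That stands; there the short window only makes the baseline covariate noisier. It does not cover yes/no absence, for which the article names only a paired test. Whether a paired test can answer a between-arm question at all is a separate matter.

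Second, self-report is a listed source and can recover absence at an earlier employer. This stands and narrows the affected group: an experienced worker who changed employer has a short window only if the earlier absence is not recovered. Self-report cannot create time at risk for someone who was not employed.

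Third, the contract requirement may select against short-term staff. It may, but it looks forward; a permanent worker hired three months ago meets it.

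Fourth, the square-root transform means that the tests may not use raw days. True, but the artefact survives it, as the simulated rates show.

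Fifth, handling of time at risk is often left to a fuller analysis plan. That would answer a complaint of missing detail. Here the unit, the window, the entry rule and the tests are all stated, and together they give a shifted before-after result.

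A reader might infer that a false rise will appear by week 48, or that the trial's absenteeism comparison as a whole is biased. The article supports neither: it gives no tenure distribution, and the arms are randomised.

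**Conclusion.** The point holds in a limited form. For workers without a fully ascertained prior year, the baseline count and yes/no cover less time than those at 48 weeks, and the paired t and McNemar tests are biased towards apparent worsening. The direction follows from the article's own rules. The size does not: it rests on the unstated share of such workers, their tenure and the distribution of days. With tenure spread over 3 to 12 months and absence in spells, the effect on the tests is small at shares of about 20% or less. It becomes material at larger shares, or if affected workers cluster near the 3-month minimum. The 44% and 76% rejection rates come from a worst case and should not be read as a forecast. This is a minor point on a secondary outcome.

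**What to change.** Record each worker's start date at the institution, and any employment gap in the year before baseline. Experience in years, already collected as descriptive data, is not time with the employer. Express days of absence per month of employment observed in the window, at baseline and at 48 weeks, and use that baseline rate as the ANCOVA covariate. Limit the 0 versus 48 week within-person comparisons, including yes/no absence, to workers with a full 12 months ascertained at baseline. Keep all randomised participants in the between-arm analysis. Report how many workers have an incomplete prior year, so that readers can judge the size. A count model with an offset, or a per-contracted-day unit, is not needed for this purpose.

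The cost is one extra date per participant, from a registry already being consulted, a few lines in the analysis plan, and somewhat fewer workers in the within-person comparisons.

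### Absenteeism looks back a full year, so at the 12-week assessment 40 of the 52 weeks counted precede the intervention and were already counted at baseline

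*Protocol article*

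**What the plan says.** Table 2 of the protocol article, under work-related variables, gives one definition of absenteeism, taken from the institution's registry and self-report: "Presence of absenteeism (yes/no), days of absence (n) and reason during last year". It gives no other window for the follow-up visits.

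The Secondary outcomes section includes absenteeism: "work-related variables [47–49] (work ability, performance, physical exertion, and absenteeism".

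Study design fixes the visits: "Assessments of primary and secondary outcomes will be conducted at baseline and at 12 weeks (post-supervised phase) and 48 weeks", counted "from the beginning of the intervention". No text exempts absenteeism from the week-12 visit.

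The Statistical analysis plan section covers both forms of the outcome. For days: "This ANCOVA will be performed separately to assess intervention effects in two time periods: 0 vs 12 weeks and 0 vs 48 weeks", with baseline as covariate. For the yes/no item: "For categorical variables, intervention effects will be analyzed with McNemar’s test".

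**The concern.** Every other outcome in Table 2 with a stated look-back uses seven days or the last month, which fits inside both follow-up intervals. Absenteeism does not. Read together, the sections ask a participant at week 12 about a year of which only the last 12 weeks fall after the start of the intervention. The other 40 weeks cannot be affected by it, and they were already counted at baseline.

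The risk is in how the week-12 result would be read. A small percentage change in annual absence, or few changes in the yes/no answer, could be taken as evidence that the programme does little for absence, when the window largely produces that picture. Work-related parameters are among the questions named in the abstract's Discussion, so the result is likely to be read.

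**Working it through.** The plan states no figure for absenteeism, so there is none to reproduce.

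**Inputs**
- Window: one year, taken as 52 weeks (Table 2).
- Visits: t = 12 and t = 48 weeks from the start of the intervention (Study design).
- Assumed, because the article does not give them: baseline taken at the start of the intervention, a constant absence rate over time, and an effect that begins at week 0.

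**1. Share of the window before the intervention: (52 − t)/52**
- Week 12: 40/52 = 76.9% before, 12/52 = 23.1% after.
- Week 48: 4/52 = 7.7% before, 48/52 = 92.3% after.

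The baseline window covers weeks −52 to 0 and the week-12 window covers weeks −40 to 12, so they share 40 weeks. The 0 vs 12 change in days therefore reduces to days in weeks 0 to 12 minus days in weeks −52 to −40.

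**2. Relative reduction in days**

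Observed rate ratio = [(52 − t) + t × RR]/52. For a true RR of 0.70:
- Week 12: (40 + 12 × 0.70)/52 = 48.4/52 = 0.931, a 6.9% reduction.
- Week 48: (4 + 48 × 0.70)/52 = 37.6/52 = 0.723, a 27.7% reduction.

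A true RR of 0.50 shows as 0.885 at week 12, and 0.80 shows as 0.954. In each case 23.1% of the true relative reduction is seen.

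**3. Yes/no item at week 12**

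Take a constant hazard and an annual risk p without intervention. The chance of at least one absence in the shared 40 weeks is 1 − (1 − p)^(40/52). These people are yes at both visits, so they can never form a discordant pair for McNemar's test. With RR = 0.70:

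| Assumed annual risk p | Yes from the shared 40 weeks | Risk difference, one-year window | Risk difference, 12-week window | Ratio |
|---|---|---|---|---|
| 20% | 15.8% | 0.0125 | 0.0148 | 0.84 |
| 40% | 32.5% | 0.0216 | 0.0320 | 0.68 |
| 60% | 50.6% | 0.0262 | 0.0530 | 0.49 |

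Set against a fully exposed year, the week-12 risk difference is 19% to 23% over these risks and RR of 0.5 to 0.7.

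**4. Days analysed by ANCOVA on baseline**

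With independent Poisson days at weekly rate λ, the one-year outcome and the one-year baseline each have variance 52λ and share a covariance of 40λ.
- Residual variance after adjustment: λ(52 − 40²/52) = λ(52 − 30.8) = 21.2λ.
- A 12-week count has variance 12λ.
- The expected between-group difference in days is the same for both, so the ratio of standardised effects is √(12/21.2) = 0.75.

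A simulation with RR = 0.70 and λ = 0.2 days per week, with and without variation in absence rate between people, gave a difference of about 0.72 days under either window. The ratios of standardised effects were 0.340/0.438 = 0.78, 0.347/0.459 = 0.76 and 0.363/0.501 = 0.72.

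**The case against.** The strongest reply is that the planned analysis of days compares mean differences, not percentages. Baseline precedes randomisation, so days in the 40 shared weeks are balanced in expectation and the expected group difference is exactly the days saved in weeks 0 to 12. This stands. A reader might infer from the 77% overlap that any effect shrinks to about a quarter, or that the week-12 result is bound to be null. For days, the article's method does not support that: the loss in standardised effect is about a quarter, not three quarters.

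A reader might also think it wrong to adjust for a baseline that shares 40 weeks with the outcome. It is not. A pre-randomisation covariate introduces no bias, and here it removes part of the noise that those weeks add.

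It can further be said that a one-year window fits collection at baseline and week 48 only, and that Fig. 1 may show exactly that. This is a fair limit. The visible text makes no such exception, but the figure was not available for this check.

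Lastly, absenteeism is one of many secondary outcomes, and the Discussion already warns that the study may lack power for them. That bears on the weight of the point. It does not make the window fit the visit.

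**Conclusion.** The point holds for the week-12 assessment, if absenteeism is collected then. By exact arithmetic, 77% of the window precedes the intervention and repeats the baseline window. The consequences differ by measure:

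- **Relative reduction in days:** cut to 23% of its true size, given a constant rate and an immediate effect.
- **Yes/no item:** insensitive, because anyone absent in the shared weeks is fixed at yes. The loss against a 12-week window grows with the annual risk, which the article does not give.
- **Absolute difference in days:** unbiased, with a standardised effect about 75% of that from a 12-week window. This rests on independent Poisson days; absence taken in spells could change the figure.

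At week 48 the overlap is 4 of 52 weeks. Calling that result contaminated would overstate it, since a true 30% reduction would still show as 27.7%. The primary outcome is unaffected. The Sample size calculation section cites relevance to absenteeism only to motivate the 1-unit pain difference, so the trial's own absenteeism result does not bear on that choice.

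**What to change.** Define follow-up absenteeism, both yes/no and days, as absence from the start of the intervention to week 12 and from the start to week 48. Take it by date from the institution's registry, already a named source, and word the questionnaire to match. Keep absence in the year before the start as the baseline covariate. If Fig. 1 does omit absenteeism at week 12, say so in Table 2; only the small week-48 overlap then remains. A count model with exposure time as an offset is an option, not needed to cure this point.

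The cost is a changed date range in the registry extraction and a reworded question, with no extra visits. Trial status reports that recruitment is still active, so the wording can still change. For participants already assessed, the registry can be re-extracted if it holds dates, which is assumed here. The downside is fewer absence events in a 12-week window, so the week-12 yes/no item will be sparser.

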**Physical fitness**		
5-repetition sit to stand test (5RSTS) [50]	Lower extremity muscle performance	Time to stand up from and sit down on a chair 5 times, mean of two attempts (seconds)
Kneeling push-up test (KPU) [51]	Upper body muscle performance	Maximum number of kneeling push-ups (repetitions)
Shirado-Ito trunk flexor endurance test (SIF) [52]	Trunk muscle performance	Maximum time in a defined trunk flexion position (seconds)

^a^Pain intensity, frequency and interference will be collected separately in 4 body locations: the low back, neck, shoulders, and hands/wrists. Average pain intensity in the low back will be the primary outcome measure

